## Abstract

**Background:**

The cervical cancer burden is high among women living in Appalachia. Cigarette smoking, a cervical cancer risk factor, is also highly prevalent in this population. This project aims to increase smoking cessation among women living in Appalachia by embedding a smoking cessation program within a larger, integrated cervical cancer prevention program.

**Methods:**

The broader program, the *Take CARE* study, is a multi-site research collaborative designed to address three risk factors for cervical cancer incidence and mortality: tobacco use, human papillomavirus (HPV) infection, and cervical cancer screening. *Break Free* is a primary care clinic-based implementation program that aims to promote smoking cessation among female smokers in Appalachia by standardizing clinical practice protocols. *Break Free* includes: (1) implementation of a tobacco user identification system in the Electronic Health Record, (2) clinic staff and provider training on the Ask, Advise and Refer (AAR) model, (3) provider implementation of AAR to identify and treat women who want to quit smoking within the next 6 months, (4) facilitated access to cessation phone counseling plus pharmacotherapy, and (5) the bundling of *Break Free* tobacco cessation with HPV vaccination and cervical cancer screening interventions in an integrated approach to cervical cancer prevention. The study spans 35 Appalachian health clinics across 10 healthcare systems. We aim to enroll 51 adult female smokers per health system (total N = 510). Baseline and follow-up data will be obtained from participant (provider and patient) surveys. The primary outcome is self-reported 12-month point prevalence abstinence among enrolled patients. All randomized patients are asked to complete follow-up surveys, regardless of whether they participated in tobacco treatment. Data analysis of the primary aims will follow intent-to-treat methodology. Secondary outcomes will assess program implementation and cost effectiveness.

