### Study overview

We are conducting a Type III hybrid effectiveness-implementation study to evaluate a multilevel smoking cessation program for women in Appalachia. Type III hybrid effectiveness-implementation study designs focus on assessing implementation outcomes while also assessing clinical outcomes associated with study implementation. Our primary study goal is to test the implementation of a clinic-based, supported tobacco cessation program in Appalachia, using measures of adoption of and fidelity to the intervention. However, we are also measuring patient-level effects of the intervention on smoking cessation rates. The evaluation will occur over 5 years and includes health system-, provider- and patient-level interventions for participating clinics from 10 health systems. The multilevel program components consist of recommendations from the *Clinical Practice Guideline* [23]. These include recommendations that health systems implement a tobacco user identification system at the clinic level (ask about, and document, smoking status) and providers advise all smokers to quit and refer those ready to quit to *Break Free* phone counseling, which provides supported smoking cessation. Notably, *Break Free* phone counseling provides treatment to women who plan to quit within six months, allowing the content to be tailored to the level of readiness to quit for each individual participant.

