##### Patient outcomes

The primary outcomes among *Break Free* patient participants include self-reported: (1) 7-day point prevalence abstinence; (2) 7-day floating abstinence during any period since last assessment; (3) prolonged abstinence (no smoking after a 2-week grace period after the quit date); and (4) at least one 24-h quit attempt. A 24-h quit attempt is an important endpoint given that it is associated with a greater likelihood of future cessation [39]. Secondary outcomes among *Break Free* participants include use of pharmacotherapy and number of counseling sessions completed.

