### Sample size and power analysis

The sample size for the primary outcome (i.e., smoking cessation among female smokers) is 51 female smokers per health system, for a total of 510 participants. This sample size is based on a two-sample test of the 7-day point prevalence abstinence at 6 months with power calculated using a standard cluster randomized design formula [44]. Assuming a 10% quit rate in the delayed group, a 25% quit rate in the early intervention group, and a conservative estimate of the intraclass correlation of 0.017, a total of 10 health systems, equally randomized to Early and Delayed Intervention groups, a total of 43 smokers per health system will provide 80% power at a two-sided significance level of 5%. The sample size was inflated to 51 smokers per health system (or 510 total) to account for an estimated 20% dropout.

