#### Patient outcomes

For all patient outcomes, we will conduct ITT analyses. We will assume that non-responders to surveys will be continued smokers.

Hierarchical (mixed) models will be used to compare smoking cessation outcomes at 6- and 12-months between female smokers in the Early and Delayed Arm health systems. Logistic models will be used for the binary outcomes, including the point prevalence, floating and prolonged abstinence, and at least one 24-h quit attempt. Subsequent analyses will adjust for patient-level characteristics in comparing smoking cessation at 6 and 12 months among patients in the Early and Delayed Arm health systems.

Mixed models will be used to assess measures of participant satisfaction with *Break Free*, using random effects for health system and primary provider. Subsequent analyses will add patient characteristics in order to evaluate whether satisfaction with the *Break Free* program differs by these characteristics.

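### The primary patient outcome is stated inconsistently (12 months in the abstract, 6 months in the sample size, four undated outcomes in the outcome list), and power is given only for the 6-month test

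*Protocol article*

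**What the plan says.** Four places in the protocol article bear on the primary patient outcome.

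- **Abstract, Methods:** "The primary outcome is self-reported 12-month point prevalence abstinence among enrolled patients". This is one outcome at 12 months.
- **Sample size and power analysis:** the recruitment target is given as follows: "The sample size for the primary outcome (i.e., smoking cessation among female smokers) is 51 female smokers per health system, for a total of 510". The next sentence gives the basis: "This sample size is based on a two-sample test of the 7-day point prevalence abstinence at 6 months". This is one outcome at 6 months, with 80% power at a two-sided 5% level.
- **Outcome evaluation, Patient outcomes:** under the label of primary outcomes, the list reads "patient participants include self-reported: (1) 7-day point prevalence abstinence; (2) 7-day floating abstinence during any period since last assessment; (3) prolonged abstinence". A fourth item follows, at least one quit attempt lasting 24 hours. No time point is attached.
- **Statistical analyses, Patient outcomes:** hierarchical models will "compare smoking cessation outcomes at 6- and 12-months between female smokers in the Early and Delayed Arm health systems". Logistic models cover all four binary outcomes. None is ranked, and neither time point is called primary.

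On the place of implementation, the Study overview says: "Our primary study goal is to test the implementation of a clinic-based, supported tobacco cessation program in Appalachia". Outcome evaluation, Provider outcomes, names adoption of Ask, Advise and Refer as the primary outcome among providers. The abstract puts program implementation under secondary outcomes.

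**The concern.** A protocol has to settle which single comparison decides whether the intervention worked. Here the current text gives different answers on the time point (6 or 12 months) and on the number of primary outcomes (one or four).

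Two things are at stake. First, the outcome that the abstract calls primary is not the one the trial was sized for, so its power is unknown. Second, nothing in the text prevents the primary result from being picked once the data are in. In that case the 5% error rate in the power statement no longer describes the claim being made.

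**Working it through.** **1. The plan's own figure.** Inputs from Sample size and power analysis: quit rates 10% and 25%, intraclass correlation 0.017, 10 health systems (5 per arm), 43 smokers per system, two-sided 5%.

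- Design effect: 1 + (43 − 1) × 0.017 = 1.714.
- Effective number per arm: 5 × 43 / 1.714 = 125.4.
- Unpooled variance: 0.10 × 0.90 + 0.25 × 0.75 = 0.2775. Standard error: √(0.2775 / 125.4) = 0.0470.
- Standardized difference: 0.15 / 0.0470 = 3.19.
- The critical value of t on 8 degrees of freedom (10 clusters − 2) is 2.306. Power is 79.9% by the shifted t and 79.7% by the noncentral t.
- Solving for cluster size at 80% power: n = 0.2775 × (2.306 + 0.889)² / 0.15² = 125.9, and m = n(1 − 0.017) / (5 − 0.017n) = 43.3.

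The stated 43 and 80% therefore reproduce. They cover one test, of 7-day point prevalence at 6 months, using the whole 5%.

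**2. Power at 12 months.** The article gives no 12-month quit rates. The same formula at 43 per system, with assumed rates, gives:

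| Assumed rates at 12 months | Power (shifted t to noncentral t) |
|---|---|
| 10% vs 25% (as for 6 months) | about 80% |
| 10% vs 22% | 62–64% |
| 10% vs 20% | 47–50% |

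**3. Error rate if the primary result may be chosen afterwards.** Each test is taken at two-sided 5%, and any positive test counts as success. The correlated cases come from 400,000 simulated draws of equally correlated normal test statistics. The correlations are assumptions; the article gives none.

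| Correlation | Point prevalence at 6 or 12 months (2 tests) | Four outcomes × two times (8 tests) |
|---|---|---|
| 0.9 | 7.0% | 11.9% |
| 0.8 | 7.8% | 15.7% |
| 0.7 | 8.3% | 19.0% |
| 0.5 | 9.1% | 25.0% |
| Independent | 1 − 0.95² = 9.75% | 1 − 0.95⁸ = 33.7% |

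The two-test column is the narrow case: the abstract and the sample size section disagree on the time point alone. The eight-test column is an upper reading, because it joins the outcome list (four outcomes, no time) to the analysis section (two times, no use of the word primary).

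**The case against.** A reader might infer that the plan declares four co-primary outcomes at two time points and so runs a 34% false-positive risk. The documents do not support that. The outcome list never says co-primary and gives no time point. The analysis section gives the time points but calls nothing primary. No passage says that any single positive test counts as success. Independence is also unrealistic: the eight tests use the same women and health systems, and the outcomes overlap. For example, a woman in prolonged abstinence at a survey is also point-prevalent abstinent then. The 34% is only a ceiling illustration.

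A reader might also infer that the lack of a multiplicity method is itself a defect, or that 6 months must be the primary time point because it is the one powered. Neither follows. Adjustment among secondary outcomes is commonly left to the analysis plan, which is not shown. The only sentence naming a single primary outcome with its time point says 12 months, and the registration record, which the article cites, cannot be seen here.

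Nor is implementation a hidden second primary. The provider outcome is openly labelled as primary among providers, and the Study overview explains that a Type III hybrid design focuses on implementation while also measuring clinical outcomes. Only the abstract's wording is out of line with those two sections.

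What survives is the core conflict. It lies in current text and concerns a choice that belongs in the protocol. An unseen analysis plan cannot make the abstract, the outcome list and the sample size section agree.

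**Conclusion.** Wrong as written. The article gives conflicting statements of the primary patient outcome, and its power statement supports only one of them, 7-day point prevalence at 6 months.

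The abstract's 12-month outcome has no stated power. It would keep about 80% if the 6-month rates held, but less if the difference narrowed, on the assumed 12-month rates shown above.

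Leaving the time point of point prevalence open is enough to lift the error rate above 5%, to about 7–9%. Leaving open all eight combinations of outcome and time would lift it to about 12–25%. Both ranges rest on assumed equal correlations of 0.9 to 0.5 and on an any-positive rule that the text neither states nor excludes.

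**What to change.** - Name one primary effectiveness outcome at one time point, Early versus Delayed Arm, two-sided 5%. Check it against the registration, and use the same wording in the abstract, the patient outcome list, the sample size section and the analysis section.
- The 6-month 7-day point prevalence is the only outcome that the document powers. If 12 months is kept, restate the power with 12-month quit rates and their justification.
- Relabel the other time point, floating abstinence, prolonged abstinence and the 24-hour quit attempt as secondary.
- Reconcile the abstract's placing of implementation under secondary outcomes with the Study overview (primary study goal) and the provider outcomes section (adoption as the provider-level primary outcome).

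The cost is mainly wording. Fewer outcomes can be claimed as primary, and a 12-month choice would carry a less favourable power figure if the 12-month difference is smaller. If the chosen outcome differs from the registered one, changing it would be a substantive amendment.

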**Discussion:**

Addressing high tobacco use rates is critical for reducing cervical cancer morbidity and mortality among women living in Appalachia. This study evaluates the implementation and effectiveness of a smoking cessation program in increasing smoking cessation among female smokers. If results demonstrate effectiveness and sustainability, implementation of this program into other health care clinics could reduce both rates of smoking and cervical cancer.

*Trial registration* NCT04340531 (April 9, 2020)

**Supplementary Information:**

The online version contains supplementary material available at 10.1186/s13722-022-00295-5.

## Background

Appalachia—a mountainous region that spans 13 states and is populated by approximately 35.7 million individuals [1]—has a higher burden of cancer than other regions in the United States (US). The cancer mortality rate in Appalachia is 10% higher than the national rate, and tobacco-related cancers are highly prevalent in this region [2–4]. Cervical cancer, a preventable condition, is 23% more prevalent in Appalachian regions and women are 25% more likely to die from cervical cancer in this region than their non-Appalachian counterparts [2–4]. These regional disparities are alarming as national incidence rates for cervical cancer have consistently been declining [5] with the growth of initiatives to address modifiable risk factors (e.g., smoking, human papillomavirus (HPV) infection rates, access to cervical cancer screening). In contrast, women in Appalachia continue to experience disparities across a multiplicity of cervical cancer risk factors [6] including disparately high smoking rates [7], low uptake of HPV vaccination [8], and low rates of cervical cancer screening [9]. To reduce cervical cancer morbidity and mortality in Appalachia, implementation research is needed to test the effectiveness and sustainability of evidence-based interventions that address cervical cancer risk factors.

Cigarette smoking is a modifiable risk factor for cervical cancer. Studies from the US, Europe, and China indicate that female smokers are at increased risk of cervical cancer and/or pre-cancerous lesions [10–12]. Smoking prevalence rates in Appalachian communities are elevated; for example, in Appalachian Ohio, 23–44% of adults report current smoking [13] and in Appalachian Kentucky current smoking prevalence is 33% rate [14]; over twice the national rate [15]. Multilevel barriers to smoking cessation exist in Appalachia. Structural determinants (e.g., high poverty rates and low educational attainment), pro-tobacco social norms, underinvestment in smoking prevention, and limited access to cessation treatment drive cessation disparities at the population level [16–18]. However, individual-level determinants including high perceived stress, cessation ambivalence, and distrust in pharmacotherapy may be additional barriers to smoking cessation in this population [19–21]. Identifying culturally acceptable, effective, and scalable interventions is critical for increasing cessation among women living in Appalachia. Undoubtedly, such interventions could have a significant, positive impact on reducing cervical cancer disparities among women living in Appalachia, in addition to the many tobacco-related chronic diseases that are widespread in this region [22].

The US Public Health Service *Clinical Practice Guideline, Treating Tobacco Use and Dependence* [23], recommends that all healthcare systems and providers systematically assess and document tobacco use, adopt motivational techniques to encourage quitting, and provide evidence-based tobacco cessation. Healthcare providers can be effective advocates for smoking cessation, with brief advice alone increasing the odds of quit attempts and abstinence [24]. However, only 50–75% of providers regularly screen patients for tobacco [25–28] and just over half of smokers report being advised to quit smoking by their providers [27–29]. As such, developing clinic-based interventions that increase the rate at which smokers are identified, advised to quit, and provided or referred for cessation treatment is critical for eliminating tobacco-related health disparities among women living in Appalachia.

Primary care clinics are an ideal setting to reach and engage women in smoking cessation treatment, as more than 70% of smokers visit a provider each year [30]. Implementing the *Clinical Practice Guideline* can be challenging, however, for primary care practices and providers, due to lack of training, limited knowledge about the recommendations, lack of patient motivation to quit, and inadequate billing and reimbursement systems [31–34]. In Appalachia, these challenges are compounded by limited access to comprehensive cessation programs that offer sustained assistance, inadequate patient education resources, and practical barriers to follow-up [35]. Barriers notwithstanding, training that targets providers’ knowledge, attitudes, and practice behaviors can increase adherence to the *Clinical Practice Guideline* [23] and increase smoking abstinence at the patient level [24]. By giving providers tools to change clinical practice behaviors, implementing provider-targeted educational interventions may be an effective strategy for reducing smoking among women living in Appalachia.

To address the high rates of both cervical cancer and smoking in Appalachian women, a transdisciplinary team of investigators developed the *Take CARE* (Clinical Avenues to Reach Health Equity) study, a multi-site research collaborative comprising four universities and participating clinics located in Appalachian counties of Kentucky, Ohio, Virginia, and West Virginia. *Take CARE* is designed to address the burden of cervical cancer incidence and mortality in Appalachia through the delivery of an integrated clinic-based cancer prevention program. Funded by the National Institutes of Health (P01CA229143), the *Take CARE* study focuses on the major causes of cervical cancer including: tobacco smoking, HPV infection, and lack of cervical cancer screening. Research in this collaborative spans both qualitative and experimental designs and involves community participation and engagement. Study endpoints include measures of intervention implementation, quality improvement processes, and client outcomes. This paper describes the study protocol for *Break Free*, one of three initiatives in the *Take CARE* study (ClinicalTrials.gov ID: NCT04340531). *Break Free* is an evidence-based smoking cessation intervention designed to address the lack of provider-led tobacco assessment and intervention in Appalachian healthcare clinics and, ultimately, increase smoking cessation rates among women living in Appalachia. The aims of this study are to determine: (1) effectiveness of the *Break Free* intervention, (2) satisfaction with the intervention, and (3) sustainability of the intervention.

## Methods

This protocol (Version 3, 11/23/2021) has been written according to the recommendations of the SPIRIT 2013 statement, a guideline that defines the standard elements of a protocol (see Additional file 1). Any modifications to the protocol are discussed during biweekly research team meetings and then communicated to the *Take CARE* Steering Committee, Institutional Review Board (IRB), trial registries, and participants as needed by IRB-approved study team members.

### Study overview

We are conducting a Type III hybrid effectiveness-implementation study to evaluate a multilevel smoking cessation program for women in Appalachia. Type III hybrid effectiveness-implementation study designs focus on assessing implementation outcomes while also assessing clinical outcomes associated with study implementation. Our primary study goal is to test the implementation of a clinic-based, supported tobacco cessation program in Appalachia, using measures of adoption of and fidelity to the intervention. However, we are also measuring patient-level effects of the intervention on smoking cessation rates. The evaluation will occur over 5 years and includes health system-, provider- and patient-level interventions for participating clinics from 10 health systems. The multilevel program components consist of recommendations from the *Clinical Practice Guideline* [23]. These include recommendations that health systems implement a tobacco user identification system at the clinic level (ask about, and document, smoking status) and providers advise all smokers to quit and refer those ready to quit to *Break Free* phone counseling, which provides supported smoking cessation. Notably, *Break Free* phone counseling provides treatment to women who plan to quit within six months, allowing the content to be tailored to the level of readiness to quit for each individual participant.

### Break Free

*Break Free* was developed through our prior work with health systems in Appalachian regions of Virginia [36] and Ohio [26, 37–39] and modified by the study team to have broad applicability across diverse primary care settings. *Break Free* is one of three initiatives in the *Take CARE* program. This overarching program also includes four cores (shared resources): Administrative, Survey and Data Collection, Intervention and Consortium, and Biostatistics and Evaluation. The Administrative Core supports the *Take CARE* program by providing leadership in program planning and development, implementing communication channels, and facilitating integration of the *Take CARE* Program cores and the three research projects. The Survey and Data Collection Core will assist initiatives with their data collection activities, develop a database of indicators and measures to be applied across all three research projects, and provide support for interactions with clinic electronic health systems and data capture. The Intervention and Consortium Core will lead efforts to develop and deliver the interventions being tested in each initiative, and maintain communications with community partners. Finally, the Biostatistics and Evaluation Core will provide investigators with a centralized resource to plan, implement, monitor, and analyze data from all three initiatives and the overall *Take CARE* program, including cost-effectiveness. Information on how each of the *Take CARE* cores will support *Break Free* project planning, implementation, data collection and analysis is described below in the context of study design, data collection, analysis, and dissemination.

Prior to launching the *Take CARE* program, lead study investigators proactively engaged executive leadership from each health system to obtain their commitment to *Take CARE* and its three initiatives, including *Break Free*. Throughout each phase of the study, lead investigators will maintain contact with health system leadership via regular communication with medical directors of participating clinics/health systems. At the end of the study, we will also present overall results from *Take CARE*, including study-specific results from *Break Free*, to the boards of participating health systems. Each initiative in *Take CARE* is also supported by a Community Advisory Board comprised of leaders from diverse community-based institutions. This Board will inform best practices for project implementation, including issues of access and barriers to uptake, as well as methods for ensuring sustainability beyond the grant funding period.

*Break Free* includes clinic, provider, and patient components (Fig. 1). During the year prior to launching *Break Free*, our team conducted community, health system, and clinic assessments; focus groups; and key informant interviews to refine the multilevel intervention components and develop materials. *Break Free* begins in the clinic with brief provider-delivered cessation counseling. During a routine medical visit, providers ask all patients about their tobacco use and document tobacco use and smoking status in the electronic health record. Providers then advise smokers to quit and assess their readiness to quit. Smokers who are ready to quit in the next 6 months receive a prescription for pharmacotherapy and a referral to the *Break Free* Enrollment Specialist. Thus, *Break Free* follows the Ask, Advise, and Refer (AAR) smoking cessation model [23].

